# 1. Background

Kaduna State is the third most populous state in Nigeria, the twelfth largest state in land mass with projected population of 7.1 million in 2016. Over the years, the state government has implemented reforms to address the health system challenges and meet the aspirations of its people for improved health. The Kaduna State Government (KDSG) espouses the bold vision of, “a state where quality health care services are available, accessible and affordable to its citizens in an equitable manner and on a sustainable basis through active participation of all individuals and communities”^[[1]](#footnote-1)^. This vision has been translated into State strategic and operational plans, including the Kaduna State Medium Term Plan, (2010-2015), Kaduna State Strategic Health Development Plan (KDSSHDP 2010-2015), Integrated Management of Childhood Illnesses, the Safe Motherhood Operational Plan (2008), Routine Immunization Strategy and Operational Plan, and the FMCH Implementation Plan. Implementation of these plans have yielded modest level of progress in health financing, delivery and outcomes in the state.

Budgetary provision was the major constraint to effective implementation and achievement of the health development plans and targets respectively. More importantly, ambitious reform plans were backed by incremental budgetary support within the framework of a Medium-Term Sector Strategy (MTSS). In the absence of adequate budgetary funding of healthcare delivery, households continued to bear the greatest financial burden, which is estimated nationally at about 70 percent of total health expenditures^[[2]](#footnote-2)^. High levels of out-of-pocket (OOP) expenditure by households limit utilization of preventive care, raise the likelihood that households are forced into seeking care only when illness if fully developed, shift the distribution of healthcare disproportionately toward curative care, and ultimately reduced efficiency of health expenditure. Financial risk protection and prepayment schemes are known to support greater and more effective utilization of healthcare services and ultimately improvement in health outcomes. But coverage of such schemes remains very low even when households are willing to pay for the needed protection from catastrophic and impoverishing healthcare expenditures.

Health accounts constitute an important healthcare policy and planning tool. In addition to aiding answers to several important policy questions, it demonstrates how healthcare resources are raised and spent, on which services by which providers and through what schemes. While Health Accounts (NHA) have been estimated at the national level for the period 1998-2014, the estimates are severely limited in answering similar policy questions at the state level. It is therefore imperative for Kaduna State to develop its own estimates of health accounts.

A household survey will be conducted in Kaduna state to provide the requisite evidence for the state governments to understand the current levels of household OOP expenditures and catastrophic expenditure levels, healthcare utilization patterns and challenges, willingness-to-pay for financial risk insurance and prepayment schemes and other relevant health behaviours. These data will contribute to estimating the Sub-National Health Account (SNHA) for Kaduna state and to inform development of appropriate policies and strategies to reduce the burden of health expenditures on poor households.

# 2. Study Objectives

In order to inform the state health accounts, this study will achieve the following objectives:

### 2.1 Primary Objective

The overall objective of the study is to estimate the current levels of financial protection on health and out of pocket (OOP) expenditure which is defined as any direct outlay by households, including gratuities and in-kind payments, to health practitioners and suppliers of pharmaceuticals, therapeutic appliances, and other goods and services whose primary intent is to contribute to the restoration or enhancement of the health status of individuals or population groups^[[3]](#footnote-3)^.

### 2.2 Secondary Objectives

The household survey would further provide insights for Kaduna state in the following areas:

1. Household utilization of health services
2. Willingness to pay for healthcare financial protection
3. Catastrophic payments for health care^[[4]](#footnote-4)^

# 3. Methodology

### 3.1 Study Design

The study will utilize a cross sectional household survey in Kaduna State of Nigeria. The survey will interview adults over 18 years to collect information on demographics, asset wealth, household expenditures, health care utilization, health care expenses and willingness to pay for healthcare financial protection. The survey will follow the general sampling strategy used for the Nigeria Demographic and Health Survey (NDHS) 2013 and the Harmonized Nigerian Living Standard Surveys (HNLSS) 2009-10. The sampling strategies of both surveys were designed to produce reliable estimates for key indicators at the national level, as well as for urban and rural areas and each of the country’s six geographical zones. Based on their sample design, we will apply state-level sampling strategy and stratify by senatorial districts, urban and rural areas.

### Sampling Frame

The sampling frame that will be used for this study include:

- List of Enumeration Areas (EA) with Sketch Maps.
- Household list in each of the sampled EAs.

Kaduna state is divided into three senatorial districts (Kaduna south, Kaduna central, Kaduna North) and 23 local government areas (LGAs), which are further subdivided into census enumeration areas (EAs). Table 1 below provides the total number of LGAs and EAs for Kaduna state and their respective average number of inhabitants in an EA. A list of EAs with their corresponding maps will be sourced from National Population Commission (NPopC). After the selection of the EAs and before the main survey, a household listing operation will be carried out in all of the selected EAs/clusters.

| **Table 1: Population and Enumeration Areas** | | |
| --- | --- | --- |
| **S/N** | **Kaduna State** | **Number** |
| 1 | Local Government Areas | 23 |
| 2 | Enumeration Areas (EAs) | 21,792 |
| 3 | Average EA size (Individuals) | 280 |
| Sources: NDHS 2013, NPopC 2006 | | |

### Sampling Procedure

A three-stage sampling method will be used in the selection of the Households:

- First stage is the stratified random sampling of the Local Government Areas (LGA).
- Second stage is the selection of the Enumeration Areas using probability proportionate to size (pps).
- Third stage is the random sampling of the households.

A stratified cluster design will be adopted for this study. The first stage will be stratified random sampling of LGAs within senatorial districts and other relevant socioeconomic parameters only to avoid some contextual issues around the LGA population figures . In the second stage, the sampled LGAs will be stratified into urban and rural areas and EAs/clusters will be selected using probability proportionate to size from each stratum of the selected LGAs. A household listing will be developed for each of the selected EAs/clusters. In the third stage, a fixed number of households will be selected in every urban and rural cluster through random sampling based on the household list.

### Sample Size

- A total number of 6 LGAs will be sampled in the state across the 3 senatorial districts.
- A total number of 17 Enumeration Areas will be covered in each sampled LGA.
- 10 Households will be selected per EA.
- 1,020 households will be canvassed in the 6 selected LGAs of Kaduna state.

Table 2 below shows the sample allocation of clusters and households by residence for Kaduna state. A total of 1,020 households and 6 LGAs will be sampled in the state. Two LGAs will be sampled from each of the 3 senatorial districts in the state with 17 EA/clusters per LGA, and 10 households per EA/cluster.

| **Table 2 Sample Selection^[[5]](#footnote-5)^** | | | |
| --- | --- | --- | --- |
| **Sample Selection** | **Kaduna State** | |  |
|  | **Urban** | **Rural** | **Total** |
| EA/Clusters | 21 | 81 | 102 |
| Households | 210 | 810 | 1020 |

### 3.4 Selection of Respondents

All adults (over 18 years) will be interviewed in selected households separately with the full survey, excluding the household characteristics, willingness-to-pay, and consumption modules, which will be administered only to the household heads. Women with children will be interviewed on their own health seeking practices as well as those of their children. Adult household members will be asked about individual characteristics (e.g., age, education level), health utilization and expenditures, and health-seeking behaviours. All available eligible adults will be interviewed upon the first visit. In the case where an eligible adult is absent, we will explore the following options: i) Call back to the household to complete the outstanding household members. (ii) Use of mobile phones to interview the eligible adult, if available and allowed by the household respondent.

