### 3.6 Questionnaires

There will be one household questionnaire with 11 sections administered to either all eligible members of households or the head of household only. The following modules and their relevant sections include:

- General information (State, LGA, EA name)
- All eligible household members
  - Verbal informed consent
  - Household roster/Individual background information (Name, sex, education, literacy, age, etc…)
  - Health seeking behaviour – inpatient and outpatient services
  - Individual expenditures on health – by inpatient and outpatient services
  - Access to health insurance
- Head of household only
  - Perceived quality of healthcare services
  - Willingness to pay for contributory health scheme
  - Household characteristics
  - Household consumption

Modules will be based on previously used questions from the NDHS and HNLSS and additional questions relevant to the context of the study as appropriate, . The questionnaire will be reviewed and finalized in coordination with the relevant stakeholders; designed and administered using an android application on mobile phones or tablets via an electronic platform; and synchronized with a web-based Survey CTO platform.

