### 3.10 Fieldwork and Monitoring

Fieldwork is expected to last for twenty-three days. All communities within selected clusters will be informed in advance of the survey and random selection of households for interview through communication with community leaders. Quality checks of instruments will be programmed prior to the start of fieldwork and monitored throughout. All data will be submitted to the central server at least once daily. There will be three main levels of data quality assurance during data collection:

1) Quality checks will be programmed into the electronic data collection software to ensure that data have been entered for all questions and skip patterns are correct;

2) The team supervisor is responsible for reviewing all completed surveys by his/her team daily;

3) Transmitted data will be verified daily by the central server supervisor. Areas prone to error will be identified for immediate action at each level for missing or outlying values. Data quality control measures during fieldwork are detailed further below.

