### 3.16 Data Analysis

A more detailed analysis plan will be developed once the survey instrument is finalized. Preliminary analyses will be performed by the authors. Stata statistical analysis software will be used for all data analysis.

Basic probability sampling weights will be calculated for each sampled cluster. Analysis will be carried out to determine the size and characteristics of the target population. We will weight for nonresponse. Descriptive characteristics of the surveyed populations will be provided, using proportions and means. These present the main findings of the study. Cross tabulation of data will be done to assess the interrelationships between two or more variables – notably assessing health expenditures, health care utilization, willingness to pay, and HIV testing across asset wealth quartiles, expenditure groupings, sex, and age.

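### Household characteristics and consumption may be answered only by the household head, so a household whose head is still not reached after call-back and phone contact cannot be classed by wealth or expenditure

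*Protocol*

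**What the plan says.** Protocol section 3.4 (Selection of Respondents) gives the full survey to every adult, "excluding the household characteristics, willingness-to-pay, and consumption modules, which will be administered only to the household heads". Section 3.6 describes one questionnaire whose sections are "administered to either all eligible members of households or the head of household only", and lists household characteristics and household consumption in the head-only group. Section 3.5 has each household acknowledge one adult as head. No section provides for an acting head or another informed adult.

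Section 3.4 does deal with absence: "In the case where an eligible adult is absent, we will explore the following options". The first option is "Call back to the household to complete the outstanding household members". The second is "Use of mobile phones to interview the eligible adult, if available and allowed by the household respondent". Section 3.5 names the head among those eligible, so both options are open for an absent head.

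The data are needed in two places. Section 3.16 tabulates the main outcomes "across asset wealth quartiles, expenditure groupings, sex, and age" and promises weighting for nonresponse without stating the level. Section 2.2 lists "Catastrophic payments for health care" as a secondary objective.

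**The concern.** Assets and household consumption are facts about the household that another adult can often report. Willingness to pay is an opinion, and there is good reason to ask it of one designated person. The protocol treats all three alike.

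Followed as written, the rule can leave a household with interviews from every other adult but no wealth class and no expenditure class. If household consumption is the denominator for catastrophic payments, that household also has no catastrophic-payment status. The analyses at stake are the wealth and expenditure gradients and one secondary objective. A later analysis plan can choose how to handle the gap, but it cannot recover answers that the form did not allow anyone to give.

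**Working it through.** **Which module carries what.** Section 3.1 promises data on asset wealth and household expenditures. In the section 3.6 list, only household characteristics and household consumption can plausibly supply them, and both are head-only. Two links are inferences: that assets sit in household characteristics, and that consumption is the catastrophic-payment denominator. The protocol states neither.

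**Planned sample.** From the Sample Size section: 6 LGAs × 17 EAs × 10 households = 1,020 households. EAs: 6 × 17 = 102, matching 21 urban + 81 rural. Households: 210 + 810 = 1,020. The protocol's figures reproduce. It states no precision target or power.

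**Households without the head modules.** Let d be the share of households whose head is never reached after call-back and phone contact. The protocol gives no value, so d is assumed.

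- Households lacking the modules = 1,020 × d
- Households per wealth quartile = 1,020 × (1 − d) / 4, against 1,020 / 4 = 255 planned
- Standard-error inflation = 1/√(1 − d)

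| d (assumed) | Lacking modules | Remaining | Per quartile | Standard error |
| --- | --- | --- | --- | --- |
| 5% | 51 | 969 | 242 | +2.6% |
| 10% | 102 | 918 | 230 | +5.4% |
| 20% | 204 | 816 | 204 | +11.8% |

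The inflation formula treats variance as proportional to 1/n. If the loss is spread evenly over EAs, clustering would make the increase smaller.

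**Bias without adjustment.** Let p be the prevalence of catastrophic payments where the head is reached and q the prevalence where he or she is not. Then the bias is p − [(1 − d)p + dq] = d(p − q). With p assumed at 15%:

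| d | q = 10% | q = 30% |
| --- | --- | --- |
| 5% | +0.25 points | −0.75 points |
| 10% | +0.5 points | −1.5 points |
| 20% | +1.0 points | −3.0 points |

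The sign depends wholly on q, on which the protocol says nothing.

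**Room for call-backs.** Section 3.8 provides three teams. Section 3.10 says "Fieldwork is expected to last for twenty-three days". If EAs are shared equally, 102 / 3 = 34 EAs per team, and 34 / 23 ≈ 1.5 EAs per team per day with no rest days. If a team works through EAs one after another, a call-back on a later day generally means a return trip.

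**The case against.** The strongest case against has five parts.

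- **Absence is provided for.** A reader might infer that any absent head costs the household its data. The protocol does not support that: call-back and phone interview cover the head, and loss arises only when both fail. This stands and limits the point. The provision is loose, however. The options are to be explored, no number of attempts is set, phone use needs permission, and section 3.5 puts the head interview at 45–60 minutes. The contingency text in section 3.11 has a label for unavailable respondents and call-back, but its content concerns weather.
- **The head-only wording may just assign modules.** It may mean only that household-level questions are not repeated for each adult, with fallback instructions left to the survey manual of section 3.8, which is not at hand. That is possible. But sections 3.4 and 3.6 both say the head only, and a form built from them would offer no other respondent.
- **Weighting can help.** It can draw on the other adults' data, the cluster and the urban or rural stratum, which is more than ordinary unit nonresponse offers. This stands, so exclusion with uncorrected bias is not a given.
- **Out-of-pocket spending is not lost.** A reader might infer that the primary out-of-pocket estimate is undermined by this rule. It is not: individual health spending is asked of all eligible members, and tables by sex and age do not need the head modules.
- **Proxy reports carry error.** A single designated respondent keeps consumption reports comparable. This is true, but a substitute used only as a last resort replaces a missing value, not a head's report, and a respondent code lets its influence be checked.

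A reader might also infer that catastrophic spending will be overstated because absent heads are labour migrants. Section 3.5 defines a household by people who usually live together, so a long-term migrant may not be its head at all, and the direction of bias is open.

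**Conclusion.** The point holds in a limited form. The protocol restricts household characteristics and consumption to the head and names no substitute. A household whose head stays unreachable therefore cannot be classed by wealth or expenditure or, by inference, assessed for catastrophic payments. At an assumed 5% to 20% of heads never reached, this affects 51 to 204 of 1,020 households and raises standard errors by roughly 2.6% to 11.8%. Neither the share lost nor the direction of bias can be established from the protocol; the bias figures above are illustrations and ignore any weighting. This is a cheap improvement to make before the form is programmed. It does not invalidate the survey.

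**What to change.** In section 3.4 and in the section 3.6 list, state that household characteristics and consumption are answered by the head or, only if the head is not reached after call-back and phone contact, by the spouse or the adult best informed on household spending. Record who answered, so that results can be shown with and without proxy reports. Keep willingness-to-pay with the head.

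While editing, align the two lists: section 3.6 also makes perceived quality of services a head-only section, which section 3.4 does not mention.

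The cost is a sentence in each section, one routing change and one respondent code in the electronic form. The downside is some proxy measurement error in the consumption reports. One gap remains: an unreached head's own health spending is still missing from the household total, so the change restores the wealth and expenditure classes more fully than the catastrophic-payment ratio.

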### 3.5 Data Collection

Interviews will be conducted at the respondent’s home at a location where he/she feels comfortable. In line with global best practice, the study instruments will be developed and reviewed by the study team to ensure that the information collected is relevant to research objectives and policy interests, thereby making the best use of the respondents’ time in the survey.

The survey is expected to last for approximately 45-60 minutes for the head of household interviews and 30 minutes for other adult household members. The survey will be administered in English with translation to Hausa in order to provide respondents with the preferred language option. Households are defined as “a person or group of person, related or unrelated, who usually live together in the same dwelling unit, have common cooking and eating arrangements, and acknowledge one adult member as the head of the household.” The head of household and men or women above 18 years present in the household on the night before the survey are eligible to be interviewed for the survey.

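### Health spending on children has no stated route into the household OOP total, and children without an eligible mother in the household have no respondent at all

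*Protocol*

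**What the plan says.** Protocol section 2.1 defines OOP by who pays, as "any direct outlay by households", and sets no age limit on the person treated. Section 5 says that some of the data will supply OOP estimates for the State Health Account.

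Section 3.4 (Selection of Respondents) sets out who is asked what:

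- Adults: "All adults (over 18 years) will be interviewed in selected households separately with the full survey".
- Content for adults: "Adult household members will be asked about individual characteristics (e.g., age, education level), health utilization and expenditures, and health-seeking behaviours".
- Children: "Women with children will be interviewed on their own health seeking practices as well as those of their children".
- The household characteristics, willingness-to-pay and consumption modules are the exception, "which will be administered only to the household heads".

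Section 3.5 gives the eligibility rule: "The head of household and men or women above 18 years present in the household on the night before the survey are eligible".

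Section 3.6 lists, among the modules for all eligible members, one on care seeking and a separate one titled "Individual expenditures on health – by inpatient and outpatient services". Household consumption is listed for the head only, and its content is not described. The questionnaire is still to be finalised.

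**The concern.** A household total is complete only if someone is asked about the spending on each member. The protocol names such a person for adults and for nobody else. If the instrument is built as the text reads, the primary OOP figure leaves out part of what it is defined to include, and the error can run only downward.

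Three consequences follow if the spending is not picked up elsewhere.

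- **State Health Account.** The OOP input would be too low.
- **Catastrophic payments (section 2.2).** If the measure sets OOP against household consumption, the numerator would leave out children while the denominator covers the whole household.
- **Comparisons by wealth and expenditure group (section 3.16).** These would be distorted wherever groups differ in number of children, because households with more children would lose more.

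Analysis cannot repair this. The weights in section 3.16 deal with cluster selection and nonresponse, not with spending that nobody was asked about. The limitations in section 6 do not mention it.

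**Working it through.** **The plan's own figure.** The only design total stated is the household sample: 6 LGAs × 17 EAs = 102 EAs, and 102 × 10 = 1,020 households. It reproduces and is not in question here.

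**Step 1: trace each type of member through the text.**

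| Member | Care seeking | Expenditure |
|---|---|---|
| Head | Own interview (3.4, 3.5) | Own interview (3.4, 3.6) |
| Other adult above 18, present the night before | Own interview | Own interview |
| Child with an eligible mother in the household | Mother (3.4) | None stated |
| Child whose mother is dead, lives elsewhere or is not herself eligible | None stated | None stated |
| Member aged exactly 18, not the head | Not clearly covered | None stated |

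**Step 2: can care-seeking practices be read to include spending?** Not easily. The next sentence of section 3.4 names expenditures and health-seeking behaviours as separate items, and section 3.6 makes them separate modules. The sentence on children matches only the care-seeking one.

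**Step 3: size.** The protocol gives neither the age structure nor the age split of spending, so everything below is assumption. Let p be the population share aged 18 or under, and r their OOP per head relative to those over 18. Their share of household OOP is

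s = p·r / (p·r + 1 − p).

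| p | r = 0.25 | r = 0.5 | r = 1.0 |
|---|---|---|---|
| 0.40 | 14.3% | 25.0% | 40.0% |
| 0.50 | 20.0% | 33.3% | 50.0% |
| 0.60 | 27.3% | 42.9% | 60.0% |

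If a fraction k of this spending is captured by another route, the understatement is (1 − k)·s:

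- k = 0: 14% to 60%.
- k = 0.5: 0.5 × 14.3% = 7% to 0.5 × 60% = 30%.
- k = 1: 0%.

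If mothers do report their children's costs, the loss is confined to children without an eligible mother. Assume these are 5% to 15% of children, with average spending. The loss is then 0.05 × 14.3% = 0.7% to 0.15 × 60% = 9%.

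**Step 4: members aged exactly 18.** Assume p = 1.5% to 2.5% and r = 0.5 to 1. The same formula gives 0.015 × 0.5 / (0.0075 + 0.985) = 0.8%, up to 0.025 / (0.025 + 0.975) = 2.5%.

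**The case against.** A reader might infer that child spending is simply absent from the total, or that OOP is understated by a definite large percentage. The protocol does not support either statement, for these reasons.

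- **Who answers is not the same as whose care is counted.** OOP is defined by payer. A parent who pays for a child's treatment makes a household outlay, and nothing confines adults' answers to their own care. The module title could mean what the person paid or what was spent on that person.
- **The consumption module is undescribed.** It may hold health outlays for the whole household.
- **The instrument is not final.** Cost items could follow the child care-seeking questions.
- **The age wording may be loose.** Over 18 may stand for 18 and over. The head is eligible with no separate age limit in section 3.5, although the household definition there calls the head an adult.
- **Any percentage is an assumed child share restated.**

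All of this stands against a claim of proven omission. It does not supply the missing rule. Without an instruction, some adults would include what they paid for children and others would not. If the consumption module does hold health outlays, adult spending may be recorded there and again in the individual module, and no rule says which is used. An unfinished questionnaire makes the correction cheap, but it does not show that the gap will be closed. The choice of respondents is settled in the protocol itself and is not a detail usually left to an analysis plan.

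**Conclusion.** The concern holds in a limited form: the rules in sections 3.4 to 3.6 do not secure coverage of the OOP total defined in section 2.1. They also leave children without an eligible mother in the household with no respondent for either topic. The result is a risk of understatement, not a demonstrated one.

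Its size is not determinable from the protocol. The lower end is zero and the upper end is the whole child share of OOP. The 14% to 60% range rests on assumed values of p and r and on no other capture, so it should be cited only as an illustration. The gap at exactly age 18 is a minor wording matter.

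The point should still be settled before fieldwork. It concerns the primary quantity, any error runs in one direction, and spending that was never asked about cannot be recovered afterwards.

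**What to change.** Amend sections 3.4 to 3.6 together.

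1. **Respondent rule.** State that utilisation and expenditure are recorded for every member on the household roster. Adults answer for themselves. For each child, one named main caregiver (mother, father, guardian or head) answers both the care-seeking and the expenditure modules, once per child.
2. **Eligibility.** Reconcile this with section 3.5, which ties eligibility of men and women above 18 to presence on the preceding night, while its household definition rests on usual residence. Say whether that presence rule limits only who is interviewed or also whose spending is counted.
3. **Source of OOP.** State whether the head's consumption module includes health outlays and which source supplies the OOP total. Tell adults whether to report what they paid or what was spent on their own care, so that caregiver reports, payers' reports and the consumption module do not count the same outlay twice.
4. **Wording.** Replace over or above 18 with 18 and over throughout, so that adults and children together cover the roster.

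The cost is protocol text, a roster loop in the electronic questionnaire, and somewhat longer interviews for caregivers in households with many children. The pre-test in section 3.7 already plans to measure completion time, so it can show whether the interview lengths in section 3.5 (45-60 minutes for heads, 30 for other adults) still hold.
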